### 7.5. Secondary analyses

The FM-UE, ARAT, NHPT, mRS, SIS-hand and SIS-participation and EQ-5D-5L at 90 days and 12 months post-stroke will be assessed using a mixed model for repeated measures or cumulative link mixed model, depending on the type of outcome measure. The outcome variable is the secondary outcome. The model includes fixed effects for the corresponding baseline scores; the stratification factor (ability versus no ability to extend one or more fingers), age, gender, stroke subtype (ischemic stroke vs. Intracerebral haemorrhage), visit (90 days; 12 months) and the interaction of treatment (sham cTBS; active cTBS) by visit and random effects for rehabilitation centre.

The length of stay will be analysed using a two-sample independent t-test.

Ipsilesional excitability will be analysed using a linear mixed model. The outcome variable is the ipsilesional RMT after the final cTBS session. The model includes fixed effects for the ipsilesional RMT before the first cTBS session, stratification factor (ability versus no ability to extend 1 or more fingers) and treatment (sham cTBS; active cTBS) and random effects for rehabilitation centre.

Contralesional excitability before the 1st, 6th and 10th cTBS session will be analysed using a mixed model for repeated measures. The outcome variable is the contralesional RMT determined before the 1st, 6th and 10th cTBS session. The model includes fixed effects for baseline RMT, cTBS session

number (1, 6 or 10) and type of treatment (sham cTBS; active cTBS) and random effects for rehabilitation centre.

Contralesional excitability after the 1st, 6th and 10th cTBS session will be analysed using a mixed model for repeated measures. The outcome variable is the contralesional MEP amplitude after cTBS. The model includes fixed effects for the contralesional MEP amplitude before cTBS, cTBS session (1, 6 or 10) and treatment (sham cTBS; active cTBS) and random effects for rehabilitation centre.

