#### 4.4 Sample size calculation

The required sample size to test our hypothesis (superiority) in two groups is 440 subjects, based on a two-sided two-sample t-test power calculation with a minimal detectable effect of 6.6 points on the FM-UE scale (10% of the maximum score of 66, a mean score at 90 days of 42 and a standard deviation of 23 (calculated from the B-STARS trial data), a statistical significance level of 0.05 and statistical power of 0.85 (G\*power 3).

A study that specifically examined clinically important differences of FM-UE scores in stroke patients found that these ranged from 4.25 to 7.25 points, depending on the different facets of UE movement. A minimal clinically important difference of 6.6 points (10% of the maximum score FM-UE score) is in line with the module 'Noninvasive brain stimulation with rTMS' for the Dutch guideline 'Ischemic stroke and intracerebral hemorrhage'.

To compensate for possible loss to follow-up, we will include 454 patients. This sample size is also sufficient to demonstrate a treatment effect on secondary outcome measures. For example, for the ARAT, which tests upper limb-specific activity, a sample size of at least 396 would be required, based on a minimal clinically important difference of 5.7 and a mean score and standard deviation of 30 and 23, respectively (calculated from the B-STARS trial data), a statistical significance level of 0.05, and a statistical power of 0.8 (gigacalculator.com).

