### **10.3 Secondary study parameter(s)**

Secondary endpoints are the FM-UE at 12 months post-stroke and the ARAT, NHPT, mRS, SIS-hand, SIS-participation and the EQ-5D at 90 days and 12 months post-stroke. These secondary endpoints are analyzed using a mixed model repeated measures or cumulative link mixed model, depending on the nature of the outcome measure. The model includes the baseline score; the stratification factor (ability versus no ability to

extend 1 or more fingers), visit (90 days and 12 months post-stroke), and the interaction of treatment (sham cTBS; active cTBS) by visit. The model includes a random effect for rehabilitation center. Additional model parameters and predefined subgroup analyses are described in the SAP.

The length of stay will be analyzed using a two-sample independent t-test.

Ipsilesional excitability will be analyzed using a linear mixed model. The outcome variable is the ipsilesional RMT after the final cTBS session. The model includes fixed effects for the ipsilesional RMT before the first cTBS session, stratification factor (ability versus no ability to extend 1 or more fingers) and treatment (sham cTBS; active cTBS) and a random effect for rehabilitation center.

Contralesional excitability before the 1st, 6th and 10th cTBS session will be analyzed using a mixed model for repeated measures. The outcome variable is the contralesional RMT determined before the 1st, 6th and 10th cTBS session. The model includes fixed effects for baseline RMT, cTBS session number (1, 6 or 10) and type of treatment (sham cTBS; active cTBS) and a random effect for rehabilitation center.

Contralesional inhibition after the 1st, 6th and 10th cTBS session will be analyzed using a mixed model for repeated measures. The outcome variable is the contralesional MEP amplitude after cTBS. The model includes fixed effects for and the contralesional MEP amplitude, cTBS session (1, 6 or 10) and treatment (sham cTBS; active cTBS) and a random effect for rehabilitation center.

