## 4. Secondary outcomes

Secondary outcomes are the score on the FM-UE at 12 months post-stroke and scores on the Action Research Arm Test, Nine Hole Peg Test, modified Rankin Scale, Barthel Index, hand and participation sections of the Stroke Impact Scale, the EuroQol-5D-5L at 90 days and 12 months post-stroke. Additional secondary outcomes are length of stay in the rehabilitation centre, change in ipsilesional and contralesional excitability and cost effectiveness. Secondary outcomes are described in Table 1.

**Table 1.** Outcome assessments

| Assessment                          | Timepoint          | Description                              | Abbreviation |
|-------------------------------------|--------------------|------------------------------------------|--------------|
| Primary outcome              |                    |                                          |              |
| Fugl-Meyer – Upper Extremity        | 90 days            | Upper extremity impairment test          | FM-UE        |
| Secondary outcomes           |                    |                                          |              |
| Fugl-Meyer – Upper Extremity        | 12 months          | Upper extremity impairment test          | FM-UE        |
| Action Research Arm Test            | 90 days, 12 months | Upper extremity activity test            | ARAT         |
| Nine Hole Peg Test                  | 90 days, 12 months | Manual dexterity test                    | NHPT         |
| Modified Rankin Scale               | 90 days, 12 months | Disability and dependence questionnaire  | mRS          |
| Barthel Index                       | 90 days, 12 months | Activities of daily living questionnaire | BI           |
| Stroke Impact Scale – Hand          | 90 days, 12 months | Hand function questionnaire              | SIS-hand     |
| Stroke Impact Scale - participation | 90 days, 12 months | Participation questionnaire              | SIS-par      |

|                             |                                                                                          |                                                                                   |          |
|-----------------------------|------------------------------------------------------------------------------------------|-----------------------------------------------------------------------------------|----------|

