## 7.7. Subgroup analyses

Predefined subgroup analyses will be based on baseline FM-UE extremity score (FM  $\leq$  20 versus FM  $>$  20); stroke subtype (ischemic stroke versus intracerebral haemorrhage); stroke location (cortical versus subcortical versus brainstem) and time to start of treatment (within 14 days versus 15 to 21 days). These analyses will be performed by including an interaction term between treatment and the previously described parameters in the linear regression model described in section 7.4.

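### Seventeen secondary tests have no hierarchy, multiplicity rule or exploratory label, yet protocol 4.4 says the trial can demonstrate secondary effects

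*Combined protocol and SAP*

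**What the plan says.** The primary endpoint is FM-UE at 90 days, active versus sham, with one named model (protocol 10.2, SAP 7.4). Protocol 4.4 sizes the trial for it at "a statistical significance level of 0.05 and statistical power of 0.85".

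For the clinical scales, SAP 7.5 says "The FM-UE, ARAT, NHPT, mRS, SIS-hand and SIS-participation and EQ-5D-5L at 90 days and 12 months post-stroke will be assessed using a mixed model", in repeated-measures or cumulative link form. Protocol 10.3 agrees: "These secondary endpoints are analyzed using a mixed model repeated measures or cumulative link mixed model, depending on the nature of the outcome measure". Both models contain a treatment-by-visit term, so each scale gives one contrast at 90 days and one at 12 months. SAP 4 adds: "Additional secondary outcomes are length of stay in the rehabilitation centre, change in ipsilesional and contralesional excitability and cost effectiveness". SAP 7.5 and protocol 10.3 give a t-test for length of stay and mixed models for ipsilesional RMT, contralesional RMT and contralesional MEP amplitude.

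SAP 7.7 adds four subgroup factors, tested in the SAP 7.4 model: "These analyses will be performed by including an interaction term between treatment and the previously described parameters in the linear regression model described in section".

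Neither document gives a testing order, a gate on the primary result, an alpha allocation or an exploratory label for any of these. Protocol 4.4 says of the 454 patients: "This sample size is also sufficient to demonstrate a treatment effect on secondary outcome measures". Its example is ARAT: difference 5.7, SD 23, significance level 0.05, power 0.8, at least 396 patients.

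**The concern.** Secondary outcomes are often taken as exploratory by default. Here the protocol works against that default: it makes a demonstration claim for secondary outcomes and backs it with a power calculation at an unadjusted 0.05. SAP 5 says the SAP specifies the hypotheses to be tested and the procedures, but no rule says how a secondary p-value is to be read.

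The practical risk is a neutral FM-UE result at 90 days followed by one nominally significant result on ARAT, SIS, mRS, EQ-5D-5L or length of stay, presented as an effect shown by the trial. The phase II case in protocol 6.4 already rests on ARAT, participation and length of stay, and protocol section 1 aims at evidence that could change a guideline. As written, nothing in the plan prevents that presentation.

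**Working it through.** **1. Count of planned tests (SAP 7.5, protocol 10.3)**
- FM-UE at 12 months: 1
- ARAT, NHPT, mRS, SIS-hand, SIS-participation and EQ-5D-5L, two visits each: 6 × 2 = 12
- Length of stay: 1
- Ipsilesional RMT, contralesional RMT, contralesional MEP amplitude: 3 (no treatment-by-session term, so one treatment test each)

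Total 17, of which 14 are clinical scales or length of stay and 3 are excitability. Cost-effectiveness is not counted. The Barthel Index is a listed secondary outcome (protocol 8.1.2, SAP 4) but has no model, so it is not counted either.

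**2. The plan's primary figure**

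Protocol 4.4 is "based on a two-sided two-sample t-test power calculation with a minimal detectable effect of 6.6 points on the FM-UE scale", with "a mean score at 90 days of 42 and a standard deviation of 23". Per arm, n = 2(1.960 + 1.036)² × 23²/6.6² = 218.1. The exact t-test solution is 219.03, so 220 per arm and 440 in total. The stated 440 reproduces at two-sided 0.05.

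**3. Chance of a false secondary result if cTBS does nothing**

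Assumptions: two-sided 0.05 per test, because 0.05 is the only level in the documents; normal test statistics with a common correlation ρ, because the documents give none. With c = 1.96 and m tests,

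P(at least one) = 1 − ∫ φ(u) [Φ((c − √ρ·u)/√(1−ρ)) − Φ((−c − √ρ·u)/√(1−ρ))]^m du.

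For results favouring cTBS only (0.025 each), drop the second Φ. To condition on a non-significant FM-UE at 90 days, multiply the integrand by one further two-sided bracket and divide the integral by 0.95; this gives the primary the same ρ with every secondary.

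At ρ = 0 the first two are 1 − 0.95^17 = 0.582 and 1 − 0.975^17 = 0.350.

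| | ρ = 0 | ρ = 0.5 | ρ = 0.8 |
|---|---|---|---|
| 17 tests, either direction | 0.58 | 0.39 | 0.21 |
| 17 tests, favouring cTBS | 0.35 | 0.19 | 0.11 |
| 17 tests, favouring cTBS, primary non-significant | 0.35 | 0.18 | 0.09 |
| 14 clinical and length-of-stay tests, favouring cTBS, primary non-significant | 0.30 | 0.16 | 0.08 |

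The benchmark is 0.05 for the first row and 0.025 for the others. The first row exceeds 0.50 only when ρ is below about 0.28.

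The four subgroup interactions, counted as one test each, form a further family at 1 − 0.95^4 = 0.19 if independent and 0.16 at ρ = 0.5.

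**4. The ARAT figure behind the demonstration claim**
- Two-sided 0.05, power 0.80: 2(1.960 + 0.842)² × 23²/5.7² = 255.6, so 256 per arm and 512 in total. The exact t-test gives 256.55, so 257 per arm and 514 in total.
- One-sided 0.05: 2(1.645 + 0.842)² × 23²/5.7² = 201.3, so 202 per arm and 404 in total. This is close to the stated 396. Protocol 4.4 does not give the sidedness for ARAT.
- Two-sided power with 440 patients (220 per arm): 5.7/(23√(2/220)) = 2.599, and Φ(2.599 − 1.960) = 0.74.
- Two-sided power with 454 patients (227 per arm): 5.7/(23√(2/227)) = 2.640, and Φ(2.640 − 1.960) = 0.75.

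**The case against.** The best defence is that this is a labelling gap. There is one primary endpoint, one contrast and one named model, and the interim analyses in protocol 10.5 cover safety only. The primary type I error is therefore intact. Neither document states that p<0.05 on a secondary counts as proof, the protocol's demonstration sentence is a remark about power, and the objectives are separated under primary and secondary headings. Formal gating is one option; cautious labelling is another. All of that stands, and it limits the point to how secondary results may be claimed.

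Four stronger readings are tempting, and the documents do not support them:
- **A false secondary finding is more likely than not.** That needs a correlation below about 0.28. Several outcomes measure the same arm and each scale is measured twice, so higher correlation is plausible.
- **Every secondary is formally tested at 0.05.** SAP 7.5 and protocol 10.3 give no level. That 0.05 would be used is an inference from protocol 4.4.
- **All 17 tests, or 19 with the Barthel Index, are potential efficacy claims.** Three concern mechanism, and protocol 8.3 marks ipsilesional excitability and contralesional inhibition as optional. The Barthel Index has no planned model, which is a separate omission.
- **The repeated-measures model creates a competing primary p-value.** FM-UE at 90 days does appear in the SAP 7.5 model, but SAP 7.4 already identifies the primary analysis.

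A both-directions figure would also overstate the harm in question: after a non-significant primary it is 0.37 at correlation 0.5, whereas only a result favouring cTBS would be read as support, and that is about half as likely.

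**Conclusion.** The point holds as a gap in how secondary results may be interpreted. Following the plan as written, a false result favouring cTBS somewhere among the 17 secondaries has probability 0.11 to 0.35 over correlations from 0.8 to 0. After a non-significant primary it is about 0.18 at correlation 0.5 and 0.09 at 0.8, roughly seven and three and a half times the 0.025 that one test carries. These figures assume no effect on any outcome, two-sided 0.05 per test and equal correlations.

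The demonstration sentence in protocol 4.4 is unsupported on a second count: at two-sided 0.05 its own ARAT example needs about 512 to 514 patients, and 440 to 454 give power of about 0.74 to 0.75. That is before any gain from baseline adjustment, which the documents do not quantify.

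**What to change.** 1. In SAP 7.5 and protocol 10.3, state that secondary and subgroup results are supportive or exploratory, reported as estimates with 95% confidence intervals and with no claim of effect based on p<0.05. Allow one exception: any short fixed sequence of key secondaries, each tested at two-sided 0.05, starting only if FM-UE at 90 days is significant and stopping at the first failure. The sponsor chooses the content and order before unblinding. Repeat the exploratory label in SAP 7.7.
2. In protocol 4.4, remove the sentence on demonstrating secondary effects or limit it to that sequence, and restate the ARAT calculation with its sidedness and the two-sided figures above.
3. As a clarification only, say in SAP 7.5 that the FM-UE 90-day estimate from the repeated-measures model supports the SAP 7.4 analysis.

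This needs no patients, visits or data and leaves the primary test and its power unchanged. The cost is that an isolated secondary result can no longer be claimed as demonstrated, and an early failure blocks later steps. For example, if ARAT at 90 days came first and the true difference were 5.7 points, about 75% power means the sequence would stop there roughly one time in four, ignoring its correlation with the primary and any gain from baseline adjustment. A Bonferroni split over all 17 tests (0.05/17 = 0.0029) would cut ARAT power to about 35 to 37%, so a short sequence or a plain exploratory label is more practical.

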## 2. Study design

B-STARS2 is a multi-centre, double-blind, randomised, sham-controlled, clinical trial.

Participants will be recruited from 16 rehabilitation centres in the Netherlands over a period of 51 months (Q2 of 2024 to Q4 of 2028). The total duration of follow-up for each participant is until one year after stroke. The total study duration is 63 months.

Baseline assessment will be performed before the start of the intervention, which must occur within 21 days after stroke onset. Follow-up assessments will be performed at 90 days (+/- 7 days) and 12 months (+/- 14 days) post-stroke (Figure 1).

The intervention consists of ten daily sessions of active or sham cTBS, delivered over the contralesional primary motor cortex, started within 21 days post-stroke and combined with regular care upper limb therapy.

Participants are randomly assigned in a 1:1 ratio to one of the two treatment groups (group A or B) using a web-based data management service. Treatment allocation is stratified by rehabilitation centre and the ability to extend one or more fingers of the affected hand.

An independent DSMB is monitoring the safety of participants of the trial. The DSMB meets at least annually. An independent statistician will perform unblinded interim analyses on all reported (serious) adverse events after 150 and 300 patients have completed the 90 days post-stroke follow-up. The independent statistician will report the outcome of the interim analyses directly to the DSMB, as well as listings of all SAE reports and unblinded aggregate summaries of data by treatment group for review in closed meetings. Feedback, blind to treatment, will be provided in written conclusions to the B-STARS2 project leaders.

[figure not shown]

**Figure 1.** Study timeline.

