## 5.2. Handling of missing data

Missing data due to loss to follow-up are assumed to be missing at random. Missing data will be reported. Prior to analysis, missing data is imputed using multiple imputation. Imputation will be performed using multiple imputation generating 500 datasets to account for inherent uncertainty, performed separately for each treatment group. This will be described in the results section of the manuscript.

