### 6.5. Intercurrent event handling

Death: Missing data in case of death will be imputed with an FM-UE score of 0.

Treatment Discontinuation: Data collected after treatment discontinuation will be included and analysed according to the treatment group to which the participant was randomized, except if treatment was discontinued before the first cTBS session.

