### 7.4. Primary analysis

The primary outcome is the FM-UE score at 90 days poststroke. The FM-UE reflects upper limb impairment on an ordinal scale from 0 (maximum impairment) to 66 points (no impairment).

The primary analysis is performed using a linear mixed model. Analysis will be performed in the primary estimand, including all randomized subjects who started at least 1 cTBS session. The outcome variable is the FM-UE score at 90 days poststroke. The model includes fixed effects for baseline FM-UE score; stratification factor (ability versus no ability to extend one or more fingers), age, gender, stroke subtype (ischemic stroke vs. intracerebral haemorrhage) and treatment (sham cTBS; active cTBS) and random effects for rehabilitation centre.

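### The secondary repeated-measures models give the baseline score one slope for both visits; a baseline-by-visit term would recover a little precision at almost no cost

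*Combined protocol and SAP*

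**What the plan says.** SAP section 7.5 assigns the scores measured at both follow-up visits to a "mixed model for repeated measures or cumulative link mixed model, depending on the type of outcome measure". On the baseline score it says "The model includes fixed effects for the corresponding baseline scores". The covariates that follow are finger extension, age, gender and stroke subtype, and the list ends with "visit (90 days; 12 months) and the interaction of treatment (sham cTBS; active cTBS) by visit and random effects for rehabilitation centre". No baseline-by-visit term appears, and the within-patient covariance structure is not stated.

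Protocol section 10.3 has the same structure, with "visit (90 days and 12 months post-stroke), and the interaction of treatment (sham cTBS; active cTBS) by visit" as its visit terms. It leaves additional model parameters to the SAP.

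Three other provisions bear on the point:

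- Visits (SAP section 2): "Follow-up assessments will be performed at 90 days (+/- 7 days) and 12 months (+/- 14 days) post-stroke". Baseline is taken before treatment starts, which is within 21 days of stroke.
- Primary analysis (SAP section 7.4): "The outcome variable is the FM-UE score at 90 days poststroke". This is a separate single-visit model.
- Missing data (SAP section 5.2): "Prior to analysis, missing data is imputed using multiple imputation". For deaths, SAP section 6.5 adds "Missing data in case of death will be imputed with an FM-UE score of 0". Both visits are therefore filled in before the model is fitted.

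**The concern.** At nominal dates, a baseline taken on day 21 lies 69 days before the 90-day visit (90 − 21) and about 344 days before the 12-month visit (365 − 21). A score from the first three weeks need not predict both results with the same slope. The listed terms assume that it does, without saying so.

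If the slopes differ, the common slope is wrong for at least one visit. Covariate adjustment then removes less of the chance variation at that visit than it could. FM-UE at 12 months is a declared secondary endpoint, and so are ARAT, NHPT, SIS and EQ-5D-5L at both visits. The stake is the width of some of their confidence intervals, not the validity of the estimates.

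**Working it through.** **The plan's own figure.** The plan states no precision for the 12-month comparisons. Its only related figure is the total of 440 for the primary endpoint (protocol section 4.4: difference 6.6, SD 23, two-sided 0.05, power 0.85). This reproduces: 219 per arm by the normal approximation, and 220 per arm (440 in total, power 0.852) by the exact t calculation. It is used below only to express losses as patients.

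**Inputs.** None of the following is in the documents; all are assumptions.

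- Baseline slope: b90 = 0.85 to 0.90 and b12 = 0.70 to 0.80.
- Residual SD: s90 and s12 each between 13 and 16.
- Residual correlation between visits: r = 0.85.
- Baseline SD: 20, so Var(baseline) = 400.
- Unstructured within-patient covariance, both visits complete, other covariates and centre left out.

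These are compatible with the stated 90-day SD of 23. The implied SD runs from √(17² + 13²) = 21.4 to √(18² + 16²) = 24.1.

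**Formulas.** With treatment by visit in the model, the effect at visit j is the difference in mean outcome minus b times the difference in mean baseline, where b is the common slope. Write S11 = s90², S22 = s12² and S12 = r·s90·s12. Then:

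- weight on the 90-day slope: w = (S22 − S12) / (S11 + S22 − 2·S12)
- common slope: b = w·b90 + (1 − w)·b12
- proportional variance loss at visit j, against separate slopes: (bj − b)² · Var(baseline) / Sjj

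**Worked case, largest loss.** Take b90 = 0.90, b12 = 0.70, s90 = 13, s12 = 16.

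- S11 = 169, S22 = 256, S12 = 0.85 × 13 × 16 = 176.8
- w = (256 − 176.8) / (169 + 256 − 353.6) = 79.2 / 71.4 = 1.109
- b = 0.70 + 1.109 × 0.20 = 0.922
- loss at 12 months = 0.2218² × 400 / 256 = 7.7%
- loss at 90 days = 0.0218² × 400 / 169 = 0.1%

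With equal residual SDs, w = 0.5 at any correlation. The same slopes with SD 13 at both visits then give 0.10² × 400 / 169 = 2.4% at each visit.

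**Results** (variance loss at 90 days / at 12 months, in %):

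| Slopes, 90 days and 12 months | SD 13 and 13 | SD 16 and 16 | SD 13 and 16 | SD 16 and 13 |
|---|---|---|---|---|
| 0.85 and 0.80 | 0.15 / 0.15 | 0.10 / 0.10 | 0.01 / 0.48 | 0.48 / 0.01 |
| 0.90 and 0.80 | 0.59 / 0.59 | 0.39 / 0.39 | 0.03 / 1.92 | 1.92 / 0.03 |
| 0.85 and 0.70 | 1.33 / 1.33 | 0.88 / 0.88 | 0.06 / 4.33 | 4.33 / 0.06 |
| 0.90 and 0.70 | 2.37 / 2.37 | 1.56 / 1.56 | 0.11 / 7.69 | 7.69 / 0.11 |

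Re-estimating the covariance with the slope misfit included did not change the weights. Under compound symmetry the weight is 0.5 throughout.

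**Scale.** A loss of 7.7% widens a confidence interval by √1.077 − 1 = 3.8% and equals about 440 × 0.0769 / 1.0769 = 31 patients. A loss of 2.4% widens it by 1.2% and equals about 10 patients.

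**Second parametrisation.** Assume SD 23 at both visits, 440 patients, between-visit correlation 0.90 and an unstructured covariance. Here a lower 12-month correlation implies a larger 12-month residual variance, so the loss falls mainly at 12 months by construction.

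| Baseline correlation, 90 days and 12 months | 12-month variance loss | Power for 6.6 points, separate slopes and common slope |
|---|---|---|
| 0.70 and 0.65 | 0.2% | not shown |
| 0.70 and 0.60 | 1.1% | 96.4% and 96.3% |
| 0.80 and 0.65 | 4.8% | 97.7% and 97.2% |

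Under compound symmetry these losses become about 0.1%, 0.4% and 1.0%. Only an extreme corner (0.85 and 0.70, between-visit correlation 0.95) reached 18%. Simulation of five settings (1,500 runs each, true effect 6.6) gave mean 12-month estimates of 6.57 to 6.62 with either model, so no bias was seen.

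**The case against.** The strongest case against is that this is a modelling preference. Nothing in the documents contradicts itself, no estimate is biased in the linear models, the primary analysis is untouched, and in typical settings power moves by a tenth of a percentage point. No passage says that the slopes differ, and if they are equal nothing is lost. All of that stands, and it limits the point to an optional improvement.

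A reader might go further and infer that the 12-month comparisons are adjusted with roughly the 90-day slope, because the two visits are highly correlated. The documents do not support that. High correlation alone does not pull the slope to either visit: equal residual SDs give the midpoint. A larger 12-month residual SD moves the slope toward the 90-day value, and a smaller one toward the 12-month value, in which case the 90-day comparison bears the loss. The SAP states neither the residual variances nor the covariance. Nor can one argue that 90 days dominates by having more data, since both visits are imputed before analysis.

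A reader might also carry the percentages over to the cumulative link models. The calculation is linear; neither the loss nor unbiasedness was examined for those models.

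**Conclusion.** The point holds as a minor one. As listed, the model has one baseline coefficient for two visits, and that costs some precision whenever the true slopes differ. Under the stated assumptions the loss in variance is between near 0 and about 8% at one visit, or 0.1 to 2.4% at each visit with equal residual SDs. It vanishes with equal slopes. A different baseline SD or a higher between-visit correlation would change these figures, and the documents supply nothing to narrow them. No conclusion of the trial is threatened.

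**What to change.** In SAP section 7.5, add the interaction of baseline score by visit to the mixed models for repeated measures of the scores taken at 90 days and 12 months. The same term may be used in the cumulative link models, but its gain there has not been quantified. Protocol section 10.3 needs no separate change, because it refers additional model parameters to the SAP.

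The cost is one phrase and one fixed-effect parameter per model, negligible with about 440 patients even if the slopes turn out equal. The change should be made before unblinding so that it cannot look data-driven. Naming the within-patient covariance structure in the same edit would be sensible but is not essential to this point.
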